## Abstract

**Background:**

Interventions promoting optimal infant and young child nutrition could prevent a fifth of under-5 deaths in countries with high mortality. Poor infant and young child feeding practices are widely documented in Kenya, with potential detrimental effects on child growth, health and survival. Effective strategies to improve these practices are needed. This study aims to pilot implementation of the Baby Friendly Community Initiative (BFCI), a global initiative aimed at promoting optimal infant and young child feeding practices, to determine its feasibility and effectiveness with regards to infant feeding practices, nutrition and health outcomes in a rural setting in Kenya.

**Methods:**

The study, employing a cluster-randomized trial design, will be conducted in rural Kenya. A total of 12 clusters, constituting community units within the government’s Community Health Strategy, will be randomized, with half allocated to the intervention and the other half to the control arm. A total of 812 pregnant women and their respective children will be recruited into the study. The mother-child pairs will be followed up until the child is 6 months old. Recruitment will last approximately 1 year from January 2015, and the study will run for 3 years, from 2014 to 2016. The intervention will involve regular counseling and support of mothers by trained community health workers and health professionals on maternal, infant and young child nutrition. Regular assessment of knowledge, attitudes and practices on maternal, infant and young child nutrition will be done, coupled with assessment of nutritional status of the mother-child pairs and morbidity for the children. Statistical methods will include analysis of covariance, multinomial logistic regression and multilevel modeling. The study is funded by the NIH and USAID through the Program for Enhanced Research (PEER) Health.

**Discussion:**

Findings from the study outlined in this protocol will inform potential feasibility and effectiveness of a community-based intervention aimed at promoting optimal breastfeeding and other infant feeding practices. The intervention, if proved feasible and effective, will inform policy and practice in Kenya and similar settings, particularly regarding implementation of the baby friendly community initiative.

**Trial registration:**

ISRCTN03467700; Date of Registration: 24 September 2014

## Background

Nutrition is critical for child survival and wellbeing. Child undernutrition is a major risk factor for ill health and mortality, contributes substantially to the burden of disease in low-income and middle-income countries (LMICs) and is associated with close to half of all child deaths [1]. This is mainly due to its influence on morbidity from the major causes of child deaths including acute respiratory illnesses, diarrhea, malaria and measles [2, 3]. Undernutrition is also a major factor for loss in disability-adjusted life years (DALYs), causing 81 million (18 %) loss in DALYs in children under 5 years [2]. Furthermore, undernutrition is associated with other adverse outcomes including compromised cognitive development, scholarly achievement and future economic productivity; and higher risk of metabolic diseases later in the life course [4].

There is a growing recognition of the importance of nutrition in the first 1000 days (during pregnancy and 2 years after birth) of life with regards to child growth, health and survival [5, 6]. Poor breastfeeding and complementary feeding practices are among the prime proximate causes of malnutrition in the first 2 years of life. Breastfeeding confers both short-term and long-term benefits to the child. It reduces morbidity and mortality among infants from infectious diseases, improves mental and motor development and protects against obesity and metabolic diseases later in the life course [5–8]. In 2002, the World Health Organization (WHO) and the United Nations Children’s Fund (UNICEF) jointly developed the global strategy for infant and young child feeding (IYCF), which aims at alleviating the burden of disease, largely associated with malnutrition, among the world’s children [9]. The WHO recommends exclusive breastfeeding in the first 6 months, to meet the infant’s nutritional requirements for optimal growth, development and health. Breastfeeding should be continued up to 2 years of age or more, while timely, nutritionally adequate, safe and appropriate complementary foods should be initiated at the age of 6 months in order to meet the developing nutritional needs of the growing infant [8]. Interventions promoting optimal breastfeeding could prevent 13 % of deaths, while those promoting optimal complementary feeding could prevent another 6 % of deaths in countries with high mortality rates [6].

In Kenya, like in other LMICs, poor maternal infant and young child nutrition (MIYCN) practices are widely documented. For example, according to the 2008/09 Kenya Demographic and Health Survey, only 32 % of children are exclusively breastfed for 6 months, improving from 13 % in 2003 [10, 11]. Additionally, only 39 % of children aged 6–23 months are fed according to the infant and young child nutrition (IYCN) guidelines [12]. Consequently, substantial levels of child malnutrition and poor child health and survival have been documented in Kenya, including high levels (35 %) of stunting among children aged under 5 years [10].

To address these poor IYCN practices, the Kenyan Government developed a strategy in 2007 to promote optimal IYCN practices nationally mirroring the WHO/UNICEF global strategy for IYCN [9, 13]. The strategy is actualized mainly through the Baby Friendly Hospital Initiative (BFHI), a global initiative that promotes breastfeeding in maternity wards [14]. However, the impact of this hospital-based initiative in LMICs like Kenya is deemed to be minimal. This is because most women, especially the poor, deliver at home, [10, 15], and MIYCN practices are greatly influenced by traditional beliefs and practices. Recognizing the need to reach women at the community level, the Division of Nutrition and Dietetics in the Ministry of Health is, therefore, considering implementing the Baby Friendly Community Initiative (BFCI), a global initiative which employs the principles of BFHI at the community level. Hard evidence on the effectiveness of BFCI and how it works best in the Kenyan context are needed to create the political buy-in, budgetary allocation and effective implementation at the national level. Though the BFCI is being implemented in both LMIC and high-income countries, little evidence from evaluation of the programs exits on its effectiveness in improving MIYCN [16]. The primary goal of the proposed intervention is to change breastfeeding practices, particularly to improve the rate of exclusive breastfeeding, which is currently low in Kenya [10], despite its documented importance in child survival [1, 5]. Specifically, the study aims to pilot implementation of BFCI to determine its feasibility and effectiveness with regards to breastfeeding and other infant feeding practices, nutrition and health outcomes in a rural setting in Kenya. Specifically, we aim to determine the effectiveness of the BFCI on: (i) the proportion of infants exclusively breastfed for the first 6 months; (ii) the rate of initiation of breastfeeding within the first hour of birth; (iii) other breastfeeding practices and maternal, infant and young child nutrition (MIYCN) knowledge, attitudes and practices; and (iv) on the nutritional and health status of children aged 6 months and below. The pilot study will also investigate the experiences, and facilitating and limiting factors, associated with the implementation of the BCFI.

The primary hypothesis is that implementation of the BFCI will improve access to counseling and support on maternal, infant and young child nutrition to mothers, and lead to higher knowledge and self-efficacy in breastfeeding practices, thereby resulting in adherence to WHO guidelines for breastfeeding. This is expected to lead to improved rates of exclusive breastfeeding for 6 months and other optimal breastfeeding practices. Eventually, improved practices are expected to impact on child nutritional and health outcomes in the community. While complementary feeding is very important, this study will not explore effectiveness of the intervention on complementary feeding. This is because due to financial limitations, we will only be able to follow children until 6 months of age, when complementary feeding is expected to be introduced.

## Methods

### Study setting

The study will be conducted in Koibatek sub-County, one of the six sub-counties in Baringo County of the North Rift region of Kenya. Residents in Koibatek practise mixed farming in an area that covers 2,306 km^2^. The total population for 2014 (as reported by sub-county Health Registry and Information Office) is 125,637 with 30,203 being women of childbearing age (15–49) and 4,799 of them being children under 1 year. Koibatek sub-county is subdivided into four administrative divisions (Eldama Ravine, Timboroa, Esageri and Torongo). The sub-county is mainly inhabited by the Tugen people, a Nilotic group whose main occupation and economic activity is mixed farming. The sub-county is served by 32 health facilities (26 dispensaries, 5 Health Centers and only 1 sub-county/district hospital) most (close to 90 %) of which are run by the government. The sub-county lies within the Rift Valley region where, according to the 2008/09 Kenya Demographic and Health Survey, the median duration of exclusive breastfeeding, was 1.7 months, which was among the highest in the country, being higher than the national rural average of 1.0 month. Slightly over a third of children are stunted, 20 % are underweight, while only a third of women deliver at a health facility [10]. Other evidence indicates that the prevalence of exclusive breastfeeding for 6 months is 32 % [17].

### Study design and randomization

The study will combine both qualitative and quantitative methods to achieve the study objectives. A formative study using participatory action research design will first be conducted. Then, a cluster randomized trial utilizing both qualitative and quantitative data collection methods will be conducted. The purpose of the formative qualitative study will be mainly to understand the local contexts and cultural factors that influence maternal nutrition, breastfeeding and other infant and young child feeding practices. This information will inform the adaptation of the intervention to the local contexts, and aid understanding of the potential barriers and facilitating factors to the implementation of the intervention. Another purpose of the formative study is to inform the finalization of quantitative data collection tools. Qualitative methods will be used at the formative stage as well as during and after the intervention to determine experiences with the intervention. Quantitative methods will mainly serve to determine effectiveness of the intervention with regards to breastfeeding practices and nutritional status.

The study will adopt a cluster-randomized trial design [18, 19]. For pragmatic purposes, community units (CUs), as defined by the government’s Community Health Strategy [20] will be used as the clusters. Thirteen CUs have been defined in the study areas. Twelve of the CUs will be randomized with half allocated to the intervention and the other half to the control arm without matching. The random sequence of allocation of the CUs to the intervention or control arm will be computer-generated. Cluster randomization is preferred over individual-level randomization to minimize contamination and for pragmatic purposes in case of future scale-up of the intervention. Randomization will be done by a data analyst who is not a primary member of the study team. Fig. 1 shows the study design schematically.

**Fig. 1 Fig1:**
[figure not shown]
Schematic of the study design

### Clusters and study populations

Twelve CUs will constitute the clusters to be included in the study. CUs are geographically defined units, mostly equal to a village (in our study setting) and usually have a population size of approximately 5000 people. The CUs are defined by the Community health Strategy, a government community-based approach where community health workers (CHWs), currently referred to as community health volunteers (CHVs) in Kenya, provide health care services to people at the community level. The reason for choosing to work with the defined CUs is pragmatic because they are administrative areas that are defined by the health care system and any intervention moving forward in the future would need to map onto these administrative units to be effective [20].

This trial will include women of reproductive age (15–49 years) who are pregnant at the time of recruitment, and their respective children from the pregnancies aged less than 6 months in Koibatek sub-county in Baringo county. These will be recruited during pregnancy on a rolling basis until the desired sample size is achieved. The target is to recruit the women as early as possible during pregnancy, particularly during the first or second trimester, so as to get as much exposure to the intervention during pregnancy as possible.

Women of reproductive age, who will have given birth before receiving at least one personalized counseling session by our trained CHWs regarding exclusive breastfeeding will be excluded. To be dropped from the analysis will be: (i) women who lose their pregnancy and/or have a still-birth; (ii) women who cannot be traced for follow-up during pregnancy; (iii) mother-child pairs of children with disability that would make their participation in the intervention difficult: for example, blind, deaf and intellectually impaired individuals or children with cleft lip.

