CHWs (including traditional birth attendants (TBAs)) and health care professionals at the lower-level health facilities (dispensaries (level 2) and health centers (level 3)) in the participating intervention CUs will be trained on the BFCI package at the beginning of the intervention followed by on-job training and mentoring through supportive supervision by the research team and the sub-county Nutrition Officer quarterly to ensure proper implementation of the BFCI at the facility and community levels. Training materials for CHWs and health professionals will include the IYCF Counseling Package developed by UNICEF in partnership with other organizations, which has been adopted by the Ministry of Health, Kenya [23]. The package is designed to equip primary health care staff to be able to support mothers and other caregivers to optimally feed their infants and young children. The CHWs and primary care staff will be equipped with infant and young child feeding counseling cards; brightly colored illustrations that depict key infant and young child feeding concepts and behaviors to share with mothers, fathers and other caregivers. The package will be adapted to include counseling messages on maternal nutrition.

As part of the BFCI package, community support groups for mothers comprising about 20 mothers per group and including other people in the community that may support the mothers such as a CHW, a community health extension worker, an older woman and a community leader, will be formed in the intervention areas. The mothers in the group will meet regularly: for example, once a month to offer each other peer-counseling and support with regards to breastfeeding and other maternal, infant and young child nutrition practices. The CHW will be the facilitator of the group. The older woman will be a model mother, carefully selected, based on knowledge and experience with infant feeding, and will be a resource for the group. The community leader, who may be the area chief or village elder, will also be a resource person particularly to offer support on administrative issues. The extension worker, who may be a skilled nurse will offer technical advice to the group.

CHWs in both intervention and control areas will be given a motivation package given as a seed grant to the whole group of CHWs to start an income-generating activity, and training on income-generating activities.

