The intervention group will also receive the BFCI package including: (i) personalized home-based counseling and support on optimal MIYCN practices by CHWs, and professional counseling of mothers by health professionals at health facilities; and (ii) formation of community support groups for mothers. In addition, they will receive MIYCN education materials. The control group will have the usual care only (Table 1). Usual care will include routine services offered to mothers and their children through the health care system including information materials regarding MIYCN, standard counseling on antenatal and postnatal care, appropriate tests during pregnancy, health facility delivery, general nutrition, hygiene, and immunization. Those in the control arm will receive routine visits by CHWs as provided for within the Community Health Strategy (usual care). Table 2 outlines the intervention package.

**Table 2 Tab2:** Services and materials provided to intervention and control groups

Intervention group	Control group
a) Distribution of MIYCN educational materials (usual care)	a) Distribution of MIYCN educational materials (usual care)
b) Supportive supervision (scheduled regular visits to assess implementation of BFCI package)	b) Supportive supervision (usual planned visits by DHMT)
c) CHW motivation package (provision of a monthly stipend (seed money for an income generating activity as a group) and training for income-generation activities as incentive)	c) CHW motivation package (Seed money for an income generating activity as a group same as in the intervention group)
d) Orientation, and continuous on job training and mentoring of the HWs and CHWs/CHEWs on BFCI package implementation	
e) Formation and support of mother support groups in the community	

*BFCI* Baby Friendly Community Initiative, *CHEWs* community health extension workers, *CHWs* community health workers, *DHMT* district health management team, *HWs* health workers, *MIYCN* maternal, infant and young child nutrition

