### Statistical analysis

Analyses will involve comparison of outcomes between the intervention group and the control group using multilevel linear logistic regression and multinomial logistic models that account for clustering.

Determination of differences between the 2 trial arms in the primary outcome (exclusive breastfeeding) will be done at month 2, month 4 and at month 6. Comparison for other outcomes such as morbidity from diarrhea and malnutrition will also be done at months 2, 4 and 6. Analyses will involve a comparison of differences in the intervention and control groups with regard to the primary outcome (exclusive breastfeeding) and secondary outcomes (other infant feeding practices, diarrhea morbidity and nutritional outcomes), controlling for baseline measures (for example, previous breastfeeding practices) and prognostic factors (for example, SES and household food security) if randomization of the clusters does not control for differences in these factors at baseline, through analysis of covariance (ANCOVA). Statistical methods to determine change will include multilevel linear regression for continuous variables (for example, z-scores, multinomial logistic regression analysis for categorical variables: for example, whether exclusively breastfed at 6 months, 4 months or 2 months [32]. Intention-to-treat analysis [33] will be applied as appropriate. Statistical analysis will mostly be done using Stata (StataCorp, College Station, TX, USA). (See Table 5 for detailed outline of data analysis plan).

**Table 5 Tab5:** Data analysis outline

Formative study				
Study objective	Primary outcome variables	Independent variable	Control variables	Type of analysis
1. To establish local contexts and norms, which contribute to maternal infant and young child nutrition (MIYCN) practices so as to customize the intervention package	Factors that influence breastfeeding and other MIYCN practices	Not applicable	Not applicable	Thematic
2. To identify facilitating factors and barriers that may influence the implementation of BFCI	Facilitating factors and barriers to the implementation of BFCI	Not applicable	Not applicable	Thematic
Cluster randomized trial				
Study objective	Outcome variables	Independent variable	Control variables	Type of analysis

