The timing of the counseling/support has been found to be important. Prenatal and postnatal breastfeeding counseling interventions, whether alone or in combination have been found effective in improving breastfeeding practices including duration of exclusive breastfeeding and any breastfeeding [36, 37]. In a systematic review of effectiveness of breastfeeding interventions that involved 38 trials [36], prenatal breastfeeding interventions significantly increased the rate of any short-term breastfeeding (1–3 months) rate by 39 % compared to the usual care while combined prenatal and postnatal interventions significantly increased both the rates of intermediate (4–5 months) and long-term (6–8 months) any breastfeeding compared to usual care by 15 % and 33 % respectively. Postnatal interventions significantly increased the rates of short-term exclusive breastfeeding (1–3 months) by 21 %. In another systematic review that involved 20 trials, only interventions with a post-natal component were found to be effective in improving breastfeeding practices while there was no evidence to suggest effectiveness of antenatal counseling/support [37]. This study, which involves home-based and facility-based counseling/support during pregnancy and 6 months following delivery, will provide further evidence on the effectiveness of combined antenatal and postnatal counseling/support on breastfeeding and other infant feeding practices.

Some limitations to this study may include bias in reporting (mothers’ self-report) of the primary outcome (exclusive breastfeeding). To counter this, data will be collected longitudinally at various time points, and a thorough questioning using 24-hour recall on what the baby was fed on will be done to ensure that as true as possible a record of infant feeding practices is obtained. It is possible that even with randomization of clusters; there will be differences in the baseline measures in the intervention and control groups by chance. Analysis methods to be adopted will control for baseline differences, if such differences are identified, but this will reduce the statistical power. Though we do not expect much loss to follow-up as we will work with a stable rural agrarian community, we plan to adopt intention-to-treat analysis to deal with potential loss to follow-up. Additionally, we have included an allowance for loss to follow-up in the sample size determination.

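### Excluding women who give birth before a session with a trained CHW selects one arm on receipt of the intervention and conflicts with the stated intention-to-treat plan

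*Protocol article*

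**What the plan says.** Clusters and study populations admits women aged 15-49 who are pregnant at recruitment, on a rolling basis. It then states that women who have "given birth before receiving at least one personalized counseling session by our trained CHWs regarding exclusive breastfeeding will be excluded". No arm is named and no counterpart for control women is given. A separate list follows of women to be dropped from the analysis: pregnancy loss or stillbirth, untraceable in pregnancy, and child disability.

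The Intervention section says that CHWs and health staff "in the participating intervention CUs will be trained on the BFCI package at the beginning of the intervention". The intervention group's package includes "personalized home-based counseling and support on optimal MIYCN practices by CHWs". For the other arm, "The control group will have the usual care only", which includes routine CHW visits under the Community Health Strategy. Counselling begins once a woman has been recruited.

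On the analysis set, Statistical analysis says "Intention-to-treat analysis [33] will be applied as appropriate". The Discussion is firmer: "we plan to adopt intention-to-treat analysis to deal with potential loss to follow-up".

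**The concern.** The randomised units are the community units, and women are recruited into them afterwards. Whether a woman has had a session before she delivers depends on how the programme performs in her cluster. A rule that uses this fact conditions on something that allocation itself determines.

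The women removed would be those identified late, those who deliver early and those who are hard to reach. Such women may well breastfeed exclusively less often. If they leave the intervention arm while their control counterparts stay, the arms differ in composition even when BFCI does nothing. If BFCI works, the comparison describes women who were reached. The trial is meant to inform national roll-out, where some women will not be reached.

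**Working it through.** **1. In which arm can the rule act?**

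- The rule needs a personalised exclusive-breastfeeding session from the study's trained CHWs before birth.
- BFCI training of CHWs is placed in intervention units, and personalised home-based CHW counselling is listed for the intervention group.
- Control women receive usual care. Its listed content includes MIYCN information materials and standard antenatal and postnatal counselling, but no such session.

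Taken literally for both arms, the rule leaves essentially no control women. The trial plans 406 women in each arm, so that cannot be intended. The remaining reading is that it acts in the intervention arm alone.

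**2. Is the condition known at enrolment?** No. Counselling follows recruitment, so a session before birth is a later event. The article does not date the randomisation. However, mobilisation before the study already refers to the two arms, and Trial status reports that the intervention has started while recruitment is still to finish. Allocation therefore precedes recruitment for at least part of the cohort.

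**3. The plan's own figures (Sample size considerations).** Inputs: 32% against 50%, two-sided 5%, 80% power, ICC 0.035, average cluster size 62.5, 10% loss.

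- Two proportions, pooled variance, no continuity correction: 117 per arm, 234 in total.
- Design effect: 1 + (62.5 - 1) × 0.035 = 3.1525.
- 234 × 3.1525 = 737.7, against the stated 738.
- 738 × 1.10 = 811.8, against the stated 812.

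The sample size reproduces and is not in dispute. With 738 / 2 = 369 per arm, the planned standard error of the difference is √[3.15 × (0.32 × 0.68 + 0.50 × 0.50) / 369] = √(3.15 × 0.4676 / 369) = 0.063, or about 6.3 points.

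**4. Spurious gain with no true effect.** Let the true rate be 32% in both arms. Let f be the share of intervention women excluded and q their own rate. Neither f nor q is in the article; both are assumptions.

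Gain = (0.32 - f·q) / (1 - f) - 0.32 = f·(0.32 - q) / (1 - f).

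| f | q = 10% | q = 20% | q = 32% |
|---|---|---|---|
| 2% | 0.02 × 0.22 / 0.98 = +0.4 points | 0.02 × 0.12 / 0.98 = +0.2 | 0 |
| 10% | 0.10 × 0.22 / 0.90 = +2.4 | 0.10 × 0.12 / 0.90 = +1.3 | 0 |
| 20% | 0.20 × 0.22 / 0.80 = +5.5 | 0.20 × 0.12 / 0.80 = +3.0 | 0 |

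**5. Effect and power if unreached women are kept.** Assume 50% in women reached and 32% in women not reached. The difference is then 18 × (1 - f) points. Power uses the method that reproduces 738.

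| f | Difference | Power at 738 | Total for 80% power, before loss |
|---|---|---|---|
| 5% | 17.1 points | 76% | about 813 |
| 10% | 16.2 | 72% | about 901 |
| 20% | 14.4 | 62% | about 1134 |

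Under the same assumptions, the comparison with the exclusion in place would report about 18 points whatever f is.

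**The case against.** **It may be an entry rule.** The sentence speaks of exclusion, and the list of women dropped from the analysis is separate. So the rule might keep women out of the cohort rather than delete them from it. That distinction is fair, and the article does not settle it. It does not rescue the rule: at either stage, entry to one arm depends on receipt of the intervention after cluster allocation.

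**Control CHWs also visit.** They do, but as usual care, and the text does not equate those visits with the required session.

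**Few women may be affected.** This stands. Recruitment aims at the first or second trimester, counselling starts at recruitment, visits become weekly after week 34, and early identification is encouraged in both arms. A share near 2%, or lower, is plausible. A reader might infer from the larger rows above that 10-20% would be excluded, or that inflation is certain. The article supports neither, and the bias vanishes if excluded women breastfeed like the rest.

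**The intention-to-treat wording is hedged.** In Statistical analysis it is. The Discussion states it as the plan, though in connection with loss to follow-up.

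**Two further inferences do not hold.** A reader might think that dropping "women who cannot be traced for follow-up during pregnancy" has the same defect. That rule names no arm, questionnaires are planned in both arms every two months, and women lost in pregnancy have no observed outcome to analyse. Unequal tracing is possible but not shown. A reader might also cite the training row of Table 2 as evidence on counselling of mothers. It concerns health workers; the evidence on mothers is in the text of the Intervention section.

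**Conclusion.** The concern holds for the counselling-before-birth exclusion. As written, the rule either empties the control arm or acts on the intervention arm alone, and the second reading conditions one arm on exposure, contrary to the stated intention-to-treat plan. This conclusion rests on the article's wording and needs no numerical assumption.

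The direction probably favours BFCI but is not certain. The size cannot be determined. Over the assumed ranges it runs from nothing to 5.5 points, the upper end being just under one planned standard error (5.5 / 6.3 = 0.87). At 2% excluded it is negligible.

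**What to change.** - Delete the exclusion of women who deliver before a counselling session.
- Define the primary analysis set by facts known at enrolment that mean the same in both arms: pregnant at recruitment and resident in a randomised community unit.
- Analyse all enrolled women with a live birth, subject to the other stated criteria, in the arm of their cluster, whatever counselling they received.
- Keep the set of women who had at least one session as a secondary analysis, labelled per-protocol.

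The edit itself is a change of wording, but it is not free if many women go unreached. At 10% unreached with no gain among them, the expected difference falls to 16.2 points and power at 738 to about 72%. The sponsor should state the share it expects to be unreached and decide whether the sample size still suffices. If that share is close to zero, the change costs almost nothing.
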